#### Randomization

Participants in the study are randomly allocated to either the adaptive training group or the non-adaptive (placebo) training group after the baseline assessment. The patients randomized to the placebo group will be offered the adaptive training after the 4-month follow-up examination. The neuropsychologist and radiologist carrying out the assessments are blinded to group adherence.

Both the adaptive and the placebo training groups undergo a 25-session standardized computerized WM training within the same time period (all participants start training/placebo at the same time), differing only in the adaptability of the training. During the training phase, weekly follow-ups by standardized phone interviews are scheduled for all participants regardless of group affiliation. After the initial training phase, the participants are examined at 1 and 4 months after finalizing their training. All participant contact is logged in order to discover potential performance bias. In addition to the research team, the patients are followed by their primary physician, who will tend to all non-trial-related issues.

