### Sample size and power calculation

Using pre-training and post-training test scores obtained by Brehmer *et al*. [47], 72 patients are needed for inclusion in the study to obtain a statistical power of 80%. Allowing for a maximum dropout rate of 20%, the number of study subjects needed for inclusion has been set to 90 patients with MCI. Power calculations are based on the primary outcome measure, which is change in WM capacity assessed by neuropsychological tests and behavioral inventories that assess WM and related functions. The statistical power measures will be calculated using Sample Power 2.0.

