### Statistical analysis

Performance gain in the assessment scores related to WM function from baseline is the primary outcome of interest. Participants' daily performance on the WM tasks within the program will be aggregated into one *t*-standardized performance score. Weekly performance scores will be used for analysis. A repeated-measure ANOVA will be conducted to investigate performance gain during the training period. One-way ANOVA will be conducted separately for the assessment criterion and transfer tasks and the rating scales of functioning, to examine potential baseline differences between the intervention and the placebo groups. To determine differences in training-related changes, a general linear mixed model with appropriate covariates will be conducted (baseline, post-training, and follow-up), and within-subject factors will be used for the cognitive tasks and assessment data. For all analyses, α levels will be set to 0.05 and effect sizes refer to partial η-square values. With regard to cerebral MRI, the DTI images will be analyzed using the software FSL with [48] to provide information on any changes in white matter microstructure with training. Automated morphometry to evaluate cortical thickness and surface area, total gray and white matter volumes, and deep nuclei volumes will be performed using the freely available FreeSurfer software program, v5.1 [49]. Complete-case analysis will be used where missing data are excluded from the analysis. A fully detailed statistical analysis will be performed before unmasking of the data.

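### The complete-case rule undercuts the planned three-visit mixed model: it can bias the arm comparison if dropout differs by arm, and it loses some precision at 1 month

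*Protocol article*

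**What the plan says.** For the difference between arms, the Statistical analysis section specifies "a general linear mixed model with appropriate covariates will be conducted (baseline, post-training, and follow-up), and within-subject factors will be used" for the cognitive and assessment data. Near the end of the same paragraph comes the only rule on missing data: "Complete-case analysis will be used where missing data are excluded from the analysis". It exempts no analysis.

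The Sample size and power calculation section states that "72 patients are needed for inclusion in the study to obtain a statistical power of 80"%, and continues: "Allowing for a maximum dropout rate of 20%, the number of study subjects needed for inclusion has been set to 90 patients with MCI". Under Randomization, "the participants are examined at 1 and 4 months after finalizing their training". The section on outcome measures and assessment procedures places the baseline assessment before randomisation, so each randomised participant should have at least a baseline score.

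**The concern.** A mixed model fitted by likelihood uses every visit that was observed and is valid when data are missing at random. Complete-case restriction gives that up. Someone seen at baseline and 1 month who misses only the 4-month visit drops out of both contrasts.

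Three things are then at stake:

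- The analysed set is no longer the randomised set.
- The 1-month effect becomes conditional on attending 3 months later.
- Observed scores that might explain dropout are thrown away.

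The Intervention section has one arm training at the limit of capacity and the other at a fixed low level, so reasons for leaving could differ by arm. The Statistical analysis section does not single out one follow-up visit, so the 1-month contrast is part of the main result. This is a rule that the document states, not a detail left for later.

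**Working it through.** **Inputs from the Protocol article.** 72 evaluable, 80% power, 20% maximum dropout, 90 enrolled, alpha 0.05, three visits.

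**Assumed, because the article does not give them.** 1:1 allocation (45 per arm), two-sided test, SD of 1 at each visit, equal correlation between visits (0.5 or 0.7), no true effect, and the dropout mechanisms below.

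**Step 1: the plan's own figure.** 72 / (1 − 0.20) = 90, which reproduces. The most that can be excluded at that rate is 90 − 72 = 18.

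**Step 2: a yardstick.** The 72 cannot be rebuilt, since no effect size or SD is stated. Solving backwards with 36 per arm: (1.960 + 0.842) × √(2/36) = 0.66 SD (0.67 with the t distribution).

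**Step 3: ceiling on the precision loss.** If all 90 attend at 1 month but only 72 are analysed, the standard error (SE) rises by √(90/72) = 1.118, about 12%.

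**Step 4: simulation.** 2000 trials per row, correlation 0.7, all 20% dropout after the 1-month visit. Where dropout depends on outcome, its log-odds change by 1.5 per SD of the 1-month score. Estimates are baseline-adjusted and in SD of a single score. CC is complete-case; ML is likelihood on all available visits.

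| Dropout | Bias, 1 month: CC / ML | Bias, 4 months: CC / ML | SE, 1 month: CC / ML | SE, 4 months: CC / ML |
|---|---|---|---|---|
| Random | 0.002 / 0.002 | 0.003 / 0.003 | 0.169 / 0.152 | 0.167 / 0.166 |
| Low scorers leave both arms | −0.001 / −0.001 | −0.001 / −0.001 | 0.163 / 0.153 | 0.163 / 0.162 |
| Low scorers leave one arm, random in the other | 0.123 / 0.001 | 0.051 / 0.001 | 0.166 / 0.151 | 0.164 / 0.163 |
| Opposite directions by arm | 0.257 / 0.001 | 0.103 / −0.001 | 0.165 / 0.151 | 0.172 / 0.175 |

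With correlation 0.5, the one-arm row gives CC bias of 0.176 at 1 month and 0.056 at 4 months.

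**Step 5: how far the size depends on assumptions.** With correlation 0.7 and dropout in the placebo arm driven by poor change at 1 month, the CC bias in a simple change score at 1 month is 0.07, 0.14 and 0.18 for log-odds slopes of 0.5, 1.0 and 1.5 per SD of change. With baseline adjustment, slopes 0.5 and 1.5 give 0.06 and 0.15. At 4 months, slope 1.5 gives 0.09 unadjusted. Taken together, one-arm dropout at correlation 0.7 gives about 0.05 to 0.18 SD at 1 month and 0.02 to 0.07 SD (baseline-adjusted) at 4 months. The sign depends on which arm loses its poorer performers.

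**Step 6: against the yardstick.** 0.05/0.66 = 8% and 0.18/0.66 = 27%. If the 0.66 is in SD of change, which is √(2 × 0.3) = 0.775 at correlation 0.7, the upper figure is (0.18/0.775)/0.66 = 35%.

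**Step 7: dropout before the 1-month visit.** If all 20% leave that early, the baseline-adjusted CC and ML estimates coincide, so nothing is recovered. Only an unadjusted completers' change score is biased there (0.06 to 0.23 SD in size when dropout differs by arm).

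**The case against.** Five points count on the other side.

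1. **Bias is not established.** It needs dropout that is related to outcome and differs by arm. Nothing in the document shows that this will happen, and the first two rows of the table show none without it. This stands. A reader might infer that the rule does bias the trial; the documents support only that it can.
2. **Timing.** The task-difficulty argument acts mainly during the 5 weeks of training, before any post-training score exists. Step 7 shows that little is recoverable from such dropouts once baseline is adjusted for. This stands, and it limits the size. It does not cover participants who attend at 1 month and miss 4 months.
3. **Power.** The 90 already allows for 20% dropout, so a reader who infers an underpowered trial would be wrong: 72 completers keep the planned 80%. This stands for power, but inflating the sample does not remove selection bias.
4. **Precision.** A loss near 17% at 1 month can appear in a single simulated scenario, but it exceeds the √(90/72) ceiling and did not reproduce. About 4% to 12% is supportable.
5. **Wording.** The sentence speaks of excluding missing data, not participants, and could mean dropping only the missing observations. That would fit the mixed model. But complete-case normally means dropping the participant, so the sentence needs rewording on either reading.

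**Conclusion.** The point holds as a should-fix. The paragraph selects a model that can keep partial records and then states a rule that, read in the usual way, discards them.

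If dropout depends on outcome in one arm only and follows the 1-month visit, the distortion is modest to material at 1 month and small at 4 months, as sized in Step 5. It is zero under random or shared-mechanism dropout. The precision cost is confined mainly to 1 month.

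These sizes rest on an assumed correlation, dropout timing and dropout strength; the upper end needs a strong dependence (a log-odds slope of 1.5 is an odds ratio near 4.5 per SD). The near-zero bias of the likelihood analysis also reflects simulated dropout that is missing at random by construction, so it is no guarantee for the trial. A reader might infer that the primary comparison is invalid unless this is changed. The documents do not support that, because they give no dropout pattern and 18 of 90 is a planning maximum, not an expected loss.

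**What to change.** Replace the complete-case sentence with a statement that:

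- the mixed model is fitted by restricted maximum likelihood to all randomised participants in their allocated arm, using every available visit;
- this analysis assumes that data are missing at random;
- complete-case analysis is kept only as a sensitivity analysis, ideally beside one that allows for data not missing at random.

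If the intention was only to omit missing observations, the same wording makes that clear.

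The cost is a few sentences and one or two extra sensitivity runs, with no new data or visits and the same main model. The article reports enrolment as ongoing and says that the detailed analysis precedes unmasking, so the change can be made without knowledge of results.

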#### Dissemination plan

The dissemination plan includes five scientific papers that will be submitted to peer-reviewed medical journals:

1. Computer-based adaptive working memory training on cognitive functioning in elderly patients with mild cognitive impairment assessed by neuropsychological tests. A randomized double-blind controlled study.

2. Does cognitive training in patients with Mild Cognitive Impairment relate to structural changes in the white and gray matter of the brain?

3. Do patients with MCI with a particular genotype for the *LMX1A* gene (i.e, AA alleles) or for *APOE* (i.e. non-ϵ4) have stronger training effects after adaptive working memory training?

4. Does computer -based working memory training have secondary effects on executive function and activities of daily living in elderly patients with MCI? A randomized, double-blind controlled study.

5. Long-term follow-up of elderly patients with mild cognitive impairment after completion of an adaptive, computerized, standardized, and intensive working memory program: neuropsychological and daily-life functioning.

The first publication will be submitted at the end of 2014, and the other articles will be submitted before the project ends in 2017. In addition, the results will be disseminated at international conferences and national forums, and in the popular press to target a wide range of groups, including researchers, healthcare providers, and health-care professionals, as well as the general public. The results will be disseminated regardless of the magnitude or direction of effect.

## Discussion

At present, there is no known cure for memory decline in the elderly or other cognitive deficits that follows MCI. Discovery of a method capable of enhancing memory, or postponing further decline in WM function in patients in the early stages of dementia, would be of great importance for a large and growing patient group.

The strengths of this trial are the extensive assessment of the participants on several levels, including gene samples, quantitative brain imaging, and neuropsychological testing. We hope the assessment will provide new and important information on the memory abilities and daily life functioning in elderly patients with MCI. This extensive assessment is relevant because of the complex nature of the etiology and behavioral outcomes of memory decline in elderly patients, and the heterogeneity of the cognitive phenotypes seen in memory clinics. The proposed study will be the first to investigate the possible mediating influence of biomarkers on the effects of cognitive training in patients with MCI. Such biomarkers may contribute in prediction of training effects. Furthermore, identification of a genetic marker to assess WM trainability would be an important finding that would allow cognitive intervention to be offered to those best able to benefit from it. This would also be of benefit to society.

Participating in this study involves no negative effects for the patients; but it may help the patients to improve their everyday functioning, and perhaps also to postpone further decline in WM function. The study also seeks to identify cognitive reserves in these patients, as such reserves seem to play an important role in the development of cognitive impairment [50]. Currently, there is a lack of knowledge of the effects of adaptive, standardized and intensive computerized WM training on individuals with MCI, and this study will be able to provide new and unique knowledge. If WM training can be shown to have positive effects on cognitive and daily-life functioning in people with MCI, a new approach to treatment of memory decline may be feasible.

## Trial status

The trial started in August 2013, and is currently enrolling participants.

## Abbreviations

BRIEF-A: Brief Rating Inventory of Executive Functions Adult version; CVLT-II: California Verbal Learning Test, second edition; D-KEFS: Delis-Kaplan Executive Function System; DEX: Behavioral assessment of the Dysexecutive Syndrome Questionnaire; IGT: Iowa Gambling Task; MCI: Mild Cognitive Impairment; Vineland: The Vineland Adaptive Behavior Scales, second edition (interview edition); WAIS-IV: Wechsler Adult Intelligence Scale, fourth edition; WMS-III: Wechsler Memory Scale, third edition.
